### Treatment of participants

The trial treatments are NAC and placebo. Participants must take 2 capsules twice per day (total 2 g of NAC) or matched placebo for 52 weeks. NAC is a GSH precursor. It is very efficiently bioavailable and is rapidly deacetylated by the liver into cysteine. Plasma cysteine levels can be rapidly increased by NAC supplementation. NAC rapidly and safely increases plasma cysteine levels, indirectly replenishing depleted systemic GSH. It is available over the counter and is approved in Australia by the Therapeutic Goods Administration (TGA) in injectable and inhalant forms for treatment of paracetamol overdose.

The NAC and placebo capsules will be identical in colour, size and shape, and will be packaged in identical bottles. NAC has a mild odour and to cover this difference between placebo and NAC, a sachet of NAC powder will be placed in all medication bottles so the same smell is present for all study capsules. Each of the treatments will be clearly labelled with a treatment number by an independent researcher. The trial products will be stored in accordance with manufacturer’s instructions which adopt Pharmaceutical Good Manufacturing Practice. Until dispensed to the participants, the trial products will be stored in a securely locked area, accessible only to authorised personnel, in accordance with GCP drug storage requirements.

Participants will be required to take the capsules as instructed during the 52 weeks of the study. At each assessment session they will be asked to return all unused capsules which will be counted for compliance rate. If less than 50 % of the capsules have been taken at any assessment point this will be viewed as non-compliance.

### Assessments

The Mini International Neuropsychiatric Interview – (MINI 6.0) will be used to confirm the diagnosis of SZ and to screen for other co-morbid conditions. The MINI 6.0 is a brief, fully structured instrument which assesses the presence of DSM-5 mood disorders, anxiety disorders, substance use disorders, and antisocial personality disorder. It employs different time frames for various disorders: current or past. The questions asked are aimed at specific psychological problems which require only ‘yes’ or ‘no’ answers. Psychometric evaluation of the MINI 6.0 shows acceptable test-retest and inter-rater reliability [25].

## Outcome and process measures

### Primary outcome measures

#### PANSS and CAINS Symptoms

The PANSS [26] and the Clinical Assessment Interview for Negative Symptoms (CAINS) [27] will be administered at baseline, 8, 24 and 52 weeks. The PANSS assesses Global Positive, Negative and General Psychopathology, and provides a well standardised method of evaluating and monitoring psychotic symptoms. The CAINS provides a more detailed examination of negative symptoms specifically. In the baseline assessment participants will be screened for the presence of negative symptoms with the PANSS and CAINS and only included in the study if they score PANSS >60 total or have at least two negative symptom items of >4.

In addition to these measures, the Calgary Depression Scale for Schizophrenia (CDSS) [28] combined with the Montgomery Asberg Depression Scale (MADRS) [29] will be administered so depression can be accounted for in the analysis of negative symptoms. The diagnostic interview and PANSS/CAINS assessment can take up to 90 min to complete. As previously noted if, after the MINI and PANSS/CAINS interviews are completed the participant is found not to fulfil the inclusion criteria the rest of the clinical interview (general measures and other symptom measures) will not be completed. The primary outcome measure for this trial will be changes to scores on the negative subscale of the PANSS and CAINS. Reductions in severity of negative symptoms in the NAC group compared with the placebo group will indicate that NAC is successfully treating these symptoms.

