**Methods:**

This study is an investigator initiated, multi-site, randomised, placebo-controlled trial. It aims to include 168 patients with clozapine-resistant SZ, divided into an intervention group (NAC) and a control group (placebo). Participants in the intervention group will receive 2 g daily of NAC. The primary outcome measures will be the negative symptom scores of the Positive and Negative Syndrome Scale (PANSS). Secondary outcome measures will include: changes in quality of life (QoL) as measured by the Lancashire Quality of Life Profile (LQoLP) and cognitive functioning as measured by the total score on the MATRICS. Additionally we will examine peripheral and cortical glutathione (GSH) concentrations as process outcomes.

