Power was calculated to detect a medium effect size of *d* = 0.5 as described in an earlier NAC and SZ paper [5] and the calculations followed the method described by Diggle et al. [23]. These calculations assumed one primary outcome measure (PANSS Negative scores), four assessment points (baseline, 8-weeks, 24-weeks, and 52-weeks follow-ups), a study-wide Type I error rate (α) of 0.01, a Type II error rate (β) of 0.10 (power of 0.90), a correlation of post-treatment scores with baseline measurements (ρ) of 0.70, employing a two-tailed statistical test. To detect the effect size of *d* = 0.5, 45 participants in each of the control and intervention groups will be required. Allowing for up to 46 % attrition (based on a 20 % dropout over the first 8 weeks and a further 30 % dropout over the ensuing 44 weeks), a total of 168 participants, or 84 in each group will be recruited. Similar attrition rates are reported in other treatment trials with treatment resistant SZ. To accommodate the required number of patients, at least 42 will need to be recruited from each of the four study sites. For the MRS component, groups of 15–20 are widely accepted as an appropriate size to permit appropriate neuroimaging analysis. As noted earlier the anticipated numbers, including drop out and ineligibility for the MRS component are 40 at baseline, 36 at 8-weeks and 52-weeks. Thus, the current study will be adequately powered for the MRS component.

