### Statistical analyses

Data will be analysed using R 3.1.2 (R Foundation for Statistical Computing, Vienna, Austria and SPSS where relevant). Intention-to-treat analyses will be employed to prevent over-estimation of efficacy. Categorical variables will be analysed using chi-squared tests (or Fisher’s exact test for small samples). A mixed-effects model, repeated measures (MMRM) approach will be used to examine the longitudinal profile of all continuous variables at weeks 8, 24, and 52 post-baseline. For all MMRM analyses, baseline scores will be used as covariates and the models will include pre-specified fixed effects of treatment, site, and time, and treatment-by-time and treatment-by-site interactions.

The MMRM modelling for the primary outcome measure – PANSS negative scores and CAINS scores – will also include baseline PANSS Positive, Negative, and General Psychopathology scores, as covariates. The secondary outcomes consist of MANSA, AQoL and MCCB global score, while the process outcomes include GSH concentrations peripherally and cortically, respectively.

Secondary analyses using Analysis of Covariance will be conducted to compare change scores during treatment and follow-up phases for all primary, secondary, and process outcomes using treatment group as a main effect with the baseline score as a covariate. Site will not be included in the analysis for the MRS data, but will be for the peripheral data. Correlational analyses will also be performed to examine for relationships between outcome variables (i.e., treatment response with cognition and GSH levels, peripherally and cortically).

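### The sample size assumes one primary outcome (PANSS negative), but the outcome and analysis sections make PANSS negative and CAINS both primary with no rule linking them, so the stated α and power are not both secured

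*Protocol article*

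**What the plan says.** Two parts of the article give one primary scale:

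- Participants section, power paragraph: "These calculations assumed one primary outcome measure (PANSS Negative scores". The design values there are "a study-wide Type I error rate (α) of 0.01", "a Type II error rate (β) of 0.10 (power of 0.90", "employing a two-tailed statistical test", and "Power was calculated to detect a medium effect size of *d* = 0.5". These lead to 45 evaluable participants per arm and, after 46% attrition, 84 per arm.
- Abstract, Methods: "The primary outcome measures will be the negative symptom scores of the Positive and Negative Syndrome Scale (PANSS". CAINS is not mentioned.

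Two parts give two primary scales:

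- PANSS and CAINS Symptoms, under the heading for primary outcomes: "The primary outcome measure for this trial will be changes to scores on the negative subscale of the PANSS and CAINS".
- Statistical analyses: "The MMRM modelling for the primary outcome measure – PANSS negative scores and CAINS scores". The secondary outcomes listed in the same section are MANSA, AQoL and the MCCB global score. CAINS is not among them, so its primary status is not a slip in a single sentence.

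The only statement about success, in the outcome section, speaks of reduced negative-symptom severity on NAC compared with placebo. It does not say on which scale.

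**The concern.** A sample size is tied to the hypothesis it was computed for. Here the α and power belong to one test on PANSS negative, while the outcome and analysis sections describe two primary scales.

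What follows depends on a rule the article does not state. If success on either scale is enough and each is tested at 0.01, the study-wide error exceeds 0.01. If both must succeed, the error is controlled but the chance of meeting the primary objective falls below 90%. If α is shared between the scales, power on PANSS negative falls. Only PANSS negative as single primary, or a fixed order led by it, keeps both stated values, and neither is written down where the primary outcome is defined.

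**Working it through.** **Inputs.** From the power paragraph: two-sided α 0.01, power 0.90, d = 0.5, ρ = 0.70, 45 evaluable per arm, attrition 46%. The article gives no correlation between PANSS negative and CAINS and no effect size for CAINS. The between-scale correlation r is therefore an assumption shown over a range, and CAINS is assumed to have the same 90% power as PANSS negative.

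**1. The plan's own figure.** With z(0.995) = 2.576 and z(0.90) = 1.282, the unadjusted size is 2 × (3.857/0.5)² = 119.0 per arm. Multiplying by a variance factor under compound symmetry gives:

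- ANCOVA, one follow-up: factor 1 − 0.49 = 0.51, so 60.7, rounded up to 61.
- ANCOVA, mean of three follow-ups: (1 + 2 × 0.70)/3 − 0.49 = 0.31, so 36.9, rounded up to 37.
- Change from baseline, mean of three follow-ups: 0.30 × 4/3 = 0.40, so 47.6, rounded up to 48.
- Change from baseline, counting four follow-ups: 0.30 × 5/4 = 0.375, so 44.6, rounded up to 45.

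No variant tried with the stated three follow-ups gives exactly 45, but 45 lies between plausible ones. It is not called wrong here, and the point does not depend on it. The attrition step does reproduce: 45/0.54 = 83.3, so 84 per arm and 168 in total.

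**2. Either scale sufficient, each at 0.01.** If independent, error = 1 − 0.99² = 0.0199. Simulating correlated normal test statistics under the null gives:

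| r (assumed) | study-wide error |
|---|---|
| 0.5 | 0.0190 |
| 0.7 | 0.0178 |
| 0.9 | 0.0151 |

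**3. Both scales required, each at 0.01.** The error stays at or below 0.01. If each scale has 90% power, joint power is 0.90² = 0.81 at r = 0. Simulation gives 0.832 at r = 0.5, 0.846 at r = 0.7 and 0.869 at r = 0.9. Joint power cannot exceed that of the weaker scale, so a smaller effect on CAINS would lower these values.

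**4. Equal α split, 0.005 each.** Take 45 per arm as giving exactly 90% at 0.01, so the expected test statistic is 3.857. With z(0.9975) = 2.807, power on PANSS negative is Φ(3.857 − 2.807) = Φ(1.050) = 0.85. Restoring 90% needs 45 × ((2.807 + 1.282)/3.857)² = 50.6, so 51 evaluable. Then 51/0.54 = 94.4, so 95 recruited per arm and 190 in total. The chance of success on at least one scale would be higher than 0.85 if NAC also moves CAINS, but the article gives no effect on CAINS from which to size that.

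**5. PANSS negative as sole primary with one contrast.** α stays at 0.01, the power claim is unchanged and N stays at 168.

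**The case against.** The best defence is that nothing in the article says either scale alone would be enough. The outcome section joins the two scales with a conjunction, and the Research aims treat negative symptoms as one primary construct. Under a both-required rule or a fixed testing order, α is kept. An analysis plan finalised before unblinding could state that rule, and a journal article is expected to leave such detail to it.

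Much of this stands. A reader might infer that the study-wide α is simply broken. The text does not support that, because α fails only under an either-scale reading. Nor does it show that the choice would be made after seeing the data.

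A reader might also count two scales at three visits as six routes to success, which would put the error at about 0.036 to 0.055 at nominal 0.01 under assumed correlations. The plan does not offer the visits as separate routes. It fits one repeated-measures model, the sample size already counts the repeated assessments, and a single overall treatment contrast adds no tests. The choice of deciding contrast is commonly left to the analysis plan. Likewise, error rates based on testing each scale at 0.05 have no footing, since the only test level given for this trial is 0.01.

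The abstract is condensed and is weak evidence on its own. The conflict rests on the power paragraph against the outcome and analysis sections.

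What the defence does not remove is the contradiction. Which outcome is primary is a protocol-level choice that the sample size depends on, and the article makes it in two different ways. Any analysis plan would have to overrule one of them.

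**Conclusion.** The point holds as an internal contradiction: one primary scale in the power paragraph and abstract, two in the outcome and analysis sections, with nothing to reconcile them. The accurate conclusion is that the stated α of 0.01 and power of 90% are not both secured.

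The size is moderate. Under an either-scale rule the error is 1.5 to 2 times the stated level. Under a both-required rule, 3 to 9 percentage points of power are lost. Under an equal split, about 5 points are lost on PANSS negative. These figures rest on assumed between-scale correlations; the second also assumes 90% power on CAINS, and the third takes 45 per arm as giving 90% at 0.01. The contradiction itself rests on no assumption.

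**What to change.** State the same primary outcome in the abstract, the power paragraph, the outcome section and the Statistical analyses section: PANSS negative alone, tested at two-sided 0.01. Name the one treatment contrast that the sample-size method assumed. That method uses all the repeated assessments, and since 45 per arm could not be matched to a single variant, the team should say which contrast produced it. Make CAINS the first key secondary, tested only if PANSS negative is significant.

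Week 52 alone should not become the primary contrast without restating power. With 45 completers per arm and ρ = 0.70, a single-visit ANCOVA has SE = √(2 × 0.51/45) = 0.151 in SD units. Then 0.5/0.151 = 3.32, and Φ(3.32 − 2.58) is about 0.77; 90% would need 61 per arm. Partial data from dropouts in the MMRM would recover some of this.

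The cost is a wording change and the loss of co-primary status for CAINS. N stays at 168 and no data are lost. Recruitment had not begun when the article was submitted, so the choice could be fixed before any outcome data existed. If the team wants to keep both scales primary, it should state the rule and restate power. An equal α split that keeps 90% on PANSS negative would need about 190 participants.

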### Secondary outcome measures

#### Quality of life

The Manchester Quality of Life Scale (MANSA) [30] is a revised and shortened version of the better known Lancashire Quality of Life Profile. It is a structured self-report interview completed with a trained interviewer that contains 16 items to provide objective and subjective ratings of quality of life in people living with SZ. It will be completed alongside the Assessment of Quality of Life (AQoL-4D) [31]. This is a 12-item questionnaire assessing quality of life across four dimensions: independent living, relationships, mental health and sense. A secondary outcome measure for this trial will be changes on these two measures of QoL. Changes indicating improvement in the NAC group specifically will indicate the impact of NAC in the predicted direction.

### Cognition

A comprehensive assessment of neurocognition across multiple domains will be performed. It will include: (1) The Wechsler Test of Adult Reading, WTAR [32], a short (1 min) word reading task that provides a measure of premorbid intelligence; (2) The Weschler abbreviated scale of IQ (WASI) [33], a 10 min assessment of current IQ; and (3) The MATRICS battery [34], an eight-domain cognitive battery that has been constructed to examine the major cognitive impairments reported in psychosis and related conditions. It assesses speed of processing, attention, verbal learning, working memory, visual learning, reasoning and problem solving, and social cognition. The MATRICS takes no longer than 80 min to complete. A scaled score can be calculated for each of the domains along with an overall general cognition score. Another secondary outcome measure of this trial will be cognitive performance. Significant improvements in cognitive performance in the NAC group over the placebo group will indicate the impact of NAC in the predicted direction.

### Process measures

#### Bloods: Peripheral glutathione

Blood samples will be collected. Biomarkers include thiols (such as GSH, cysteine, cysteinyl-glycine, NAC) and corresponding disulphides (such as glutathione disulphide (GSSG) and cystine). This collection for biomarker analyses will occur at baseline, 8, 24 and 52 weeks, to monitor for peripheral changes.

### Magnetic Resonance Spectroscopy (MRS): Cortical glutathione

A sub-set of participants (*N* = 42) will be invited to undergo MRI scans. Scans will be acquired using Swinburne University’s (Melbourne) Siemens Trio 3 Tesla MRI (Siemens AG, Munich, Germany). Participants will spend 1 hour in the scanner. An MRS sequence enables the measurement of levels of metabolites found in the brain. The cerebral metabolites that will be measured in the current study are creatine (Cre) and GSH. MRS voxels will be prescribed in the medial prefrontal cortex (mPFC) and will be 50 × 30 × 30 mm. The voxel will be positioned using an axial T1-weighted gradient-echo image. Spectral processing with be performed using *LCModel* software which permits us to calculate GSH concentrations (calculated in reference to total Cre).

### Safety

The Adverse Symptom Checklist (known as SAFTEE) is a 21-item scale that rates the presence and severity (0 = not present to 3 = severe) of common symptoms associated with psychotropic treatments. As well as being assessed at baseline, 8, 24 and 52 weeks, a telephone assessment at 2, 4 and 6 weeks will also be completed using this assessment. Clozapine levels will be measured at baseline and 8, 24 and 52 weeks to ensure adherence and to ascertain any pharmacokinetic interactions with NAC (we do not expect any such effects as the kinetics of the two agents do not suggest interaction). As well as clozapine levels, hepatic and renal function, full blood count, other metabolic information and electrocardiogram (ECG) will be performed as part of routine clozapine monitoring will be maintained according to local requirements.

## Data management

Data will first be entered into a handwritten patient file and later entered into a computerised database designed for this trial. Double data entry will be completed for 10 % of all study files.

### Statistical analyses

Data will be analysed using R 3.1.2 (R Foundation for Statistical Computing, Vienna, Austria and SPSS where relevant). Intention-to-treat analyses will be employed to prevent over-estimation of efficacy. Categorical variables will be analysed using chi-squared tests (or Fisher’s exact test for small samples). A mixed-effects model, repeated measures (MMRM) approach will be used to examine the longitudinal profile of all continuous variables at weeks 8, 24, and 52 post-baseline. For all MMRM analyses, baseline scores will be used as covariates and the models will include pre-specified fixed effects of treatment, site, and time, and treatment-by-time and treatment-by-site interactions.

The MMRM modelling for the primary outcome measure – PANSS negative scores and CAINS scores – will also include baseline PANSS Positive, Negative, and General Psychopathology scores, as covariates. The secondary outcomes consist of MANSA, AQoL and MCCB global score, while the process outcomes include GSH concentrations peripherally and cortically, respectively.

Secondary analyses using Analysis of Covariance will be conducted to compare change scores during treatment and follow-up phases for all primary, secondary, and process outcomes using treatment group as a main effect with the baseline score as a covariate. Site will not be included in the analysis for the MRS data, but will be for the peripheral data. Correlational analyses will also be performed to examine for relationships between outcome variables (i.e., treatment response with cognition and GSH levels, peripherally and cortically).

Although the attrition rate is not expected to vary by treatment condition, we will attempt to identify key predictors of attrition status (i.e., demographic and baseline clinical characteristics) and test for differences between conditions. Assuming the data are missing at random, several procedures offer effective approaches that may deal with attrition, statistically. Maximum likelihood models, with time as a random variable, allow the use of all available data from all assessments, reducing bias and increasing power [35]. There are three other accepted approaches to analyses with missing data: (a) multiple imputation procedures that utilise the expectation-maximization (EM) algorithm with bootstrap estimates of standard errors; (b) raw maximum-likelihood analysis; or (c) multiple-group structural equation or latent growth modelling [23]. For manifest variable models, these methods produce virtually identical results and will be used to address attrition. In general, the application of these missing data procedures can provide unbiased estimates, even in the face of substantial attrition.

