### Participants

Forty-two patients will be recruited from each of the sites, with a total target of 168 participants aged 18–65 years meeting DSM-5 criteria for SZ. Investigators at each site will be responsible for recruiting participants through advertising and engagement with clozapine clinics associated with their site. As we are interested in clozapine patients who have residual symptoms, all potential participants will be screened and assessed for eligibility. The following inclusion criteria are to be adhered to: (1) Aged 18–65 years; (2) Confirmed diagnosis of SZ via clinical interview; (3) Have been on clozapine at an adequate dose for at least 6 months, ascertained by a current serum level of >350 mcg/L and with residual symptoms (see 4.)^1^; (4) Have a PANSS score of ≥60 or at least two negative symptom items of >4^2^; (5) Have the capacity to provide consent to the study; and (6) Be utilising effective contraception (i.e., oral or barrier contraception) if female and of childbearing age. In addition, the following exclusion criteria will be applied: (1) Participants who are currently taking NAC; (2) Participants who are allergic to NAC or any component of the preparation; (3) Participants who are currently prescribed nitro-glycerine (significant potential interaction with NAC); (4) Participants who have diabetes mellitus and on insulin replacement (including exenatide) (moderate interaction); (5) Participants taking Aralen (moderate interaction); (6) Participants who regularly take >200 mg/day selenium (moderate interaction); (7) Participants who regularly take anticoagulants (moderate interaction) (excluding aspirin and non-steroidal anti-inflammatories); (8) Change in medication from clozapine to another antipsychotic; (9) Participants with known primary or secondary autoimmune disorders; (10) Recent gastrointestinal ulcers; (11) Recent renal stones; and (12) Females who are pregnant or lactating.

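### The primary MMRM carries a fixed treatment-by-site interaction although the trial hypothesises and powers one overall effect, so the treatment term is the overall effect only through a marginal contrast

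*Protocol article*

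**What the plan says.** All statements are in the protocol article.

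- **Model (Statistical analyses).** The scope is general: "For all MMRM analyses, baseline scores will be used as covariates". The terms common to these analyses are then listed: "the models will include pre-specified fixed effects of treatment, site, and time, and treatment-by-time and treatment-by-site interactions".
- **Primary outcome (same section).** The model for PANSS negative and CAINS scores "will also include baseline PANSS Positive, Negative, and General Psychopathology scores, as covariates". This adds covariates to the common model and removes nothing, so the interaction stays in the primary analysis.
- **Question (Research aims).** The hypothesis is that NAC is superior to placebo for negative symptoms in patients taking clozapine. It is a single overall claim, not one per site.
- **Sample size (Participants).** The calculation is for one treatment effect of d = 0.5, with "a study-wide Type I error rate (α) of 0.01", two-tailed, power 0.90 and ρ = 0.70, giving 45 per group. No allowance for site-specific effects is mentioned.
- **Sites (Participants).** "Forty-two patients will be recruited from each of the sites"; the sample-size paragraph has it as "at least 42 will need to be recruited from each of the four study sites".

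The article does not say which contrast, coding or site weighting carries the primary test.

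**The concern.** When treatment-by-site and treatment-by-time are both fixed effects, no single coefficient is the treatment effect. What the treatment term estimates depends on the coding, the visit and the site weights. Under reference coding, the default in R ("Data will be analysed using R 3.1.2"), it is the NAC-placebo difference at the reference site and reference visit. If that coefficient were reported as the main result, the trial would answer a question about one of four sites, with much less information. If site effects differ, the answer could also be different. In a check simulation with assumed site effects of 0.2, 0.5, 0.6 and 0.7 (mean 0.5), the reference-coded coefficient averaged 0.19 while the equal-site contrast averaged 0.50.

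A marginal contrast with equal site weights returns to the overall question. It gives a small site the same say as a large one, however, so it loses precision when sites end up unequal. Site as a main effect already adjusts for differences in level between sites, and the interaction adds nothing to the estimate of the overall effect.

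**Working it through.** **Inputs from the protocol article (Participants).** d = 0.5 with SD 1, ρ = 0.70, α = 0.01 two-sided, power 0.90, 45 evaluable per arm, four sites of 42, post-baseline visits at weeks 8, 24 and 52.

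**Assumptions.** ρ = 0.70 between every pair of visits (the article gives it only between baseline and post-treatment scores); 45 per arm with complete data; equal arms within each site; no site-by-treatment-by-time term, as in the stated model.

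**1. The plan's own figure.** Covariance adjustment at one visit gives n = 2 × ((2.576 + 1.282)/0.5)² × (1 − 0.70²) = 119.0 × 0.51 = 60.7 per arm, not 45. Of the other repeated-measures forms tried at this α, the nearest is the mean of three post-baseline visits minus baseline, at 47.6. The inflation step does reproduce: 45/(1 − 0.46) = 83.3, so 84 per group and 168 in total. The starting power below is therefore 0.75 rather than 0.90. That gap is not caused by the interaction, and the ratios of standard errors and variances do not depend on it.

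**2. Residual covariance after baseline adjustment.**
- Variance at one visit: 1 − 0.49 = 0.51.
- Covariance between two visits: 0.70 − 0.49 = 0.21.
- Variance of the mean of three visits: (0.51 + 2 × 0.21)/3 = 0.31.

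**3. Without the interaction.** The variance of the treatment effect at a visit is 0.51 × 2/45 = 0.02267, so SE = 0.151. Noncentral-t power (88 df) at α = 0.01 is 0.75.

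**4. Reference-coded coefficient, equal sites.** The effect at one site and visit is the overall effect at that visit plus that site's deviation. The deviation is common to all visits, so it is estimated from the three-visit mean. For one of four equal sites its variance is (4 − 1) × 0.31 × 2/45.
- Total: (0.51 + 3 × 0.31) × 2/45 = 1.44 × 2/45 = 0.0640, so SE = 0.253.
- SE ratio: √(1.44/0.51) = 1.68.
- Power at α = 0.01: 0.26.

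**5. Equal-site marginal contrast.** Let VR = (N/16) × Σ(1/n_s), with N = 168. The variance relative to the model without interaction is 1 + (0.31/0.51) × (VR − 1).

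| Site sizes | VR | Variance ratio | Power, α = 0.01 |
|---|---|---|---|
| 42/42/42/42 (planned) | 1.00 | 1.00 | 0.75 |
| 60/50/38/20 (assumed) | 1.186 | 1.11 | 0.70 |
| 70/56/28/14 (assumed) | 1.463 | 1.28 | 0.62 |

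The unequal splits are applied proportionally to the 45 per arm. Direct inversion of the generalised least squares information matrix for the stated three-visit model gives the same values as steps 3 to 5.

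**The case against.** The best defence is that the harm is conditional. The article does not say that the raw coefficient will carry the primary test. A careful analyst would take a marginal contrast, and contrast, coding and weights are details that a condensed article commonly leaves to the SAP. With 42 at each site the marginal contrast is the overall effect at no cost. The section also plans secondary ANCOVAs with treatment as a main effect and states no site interaction for them. All of this stands. It does not remove the point, because the interaction itself is stated for the primary model: an SAP could name a contrast, but could not drop the term without departing from this text.

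Stronger readings that the documents do not support:

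- **The standard error doubles and power falls to 0.14.** A reader might infer this by counting about 11 completers per arm at one site. That describes a single-visit model. In the stated model the site deviation draws on all three visits, which gives 1.68 and 0.26.
- **The equal-site average is inefficient in itself.** It is not at 42 per site. The single-visit penalties of 19% and 46% at the two assumed splits also overstate the loss with three visits, which is 11% and 28%.
- **R and SPSS will give conflicting results for one model.** The article names R, with SPSS where relevant. It does not say that both fit the same model.
- **Post-baseline depression will be a covariate.** The outcome section says only that depression is measured "so depression can be accounted for in the analysis of negative symptoms". It does not propose adjustment for later values.

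**Conclusion.** The concern holds in a limited form. The interaction is fixed in the primary MMRM and does not fit a trial that asks and powers one overall question. The damage depends on what is reported. It is serious if the reference-coded coefficient is used (SE about 1.7 times larger, power 0.26 against 0.75). It is nil for an equal-site marginal contrast at the planned 42 per site, and modest to moderate for that contrast if sites become unequal.

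Unequal numbers are possible, since the site target is a minimum and up to 46% attrition is allowed for, but the splits used here are assumptions and not forecasts. The power figures also rest on a correlation of 0.70 between all visits and on 45 complete participants per arm. More participants would remain at week 8 (84 × 0.80 = about 67 per arm under the stated dropout), so absolute power at that visit would be higher than shown with or without the interaction.

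**What to change.** In Statistical analyses, remove treatment-by-site from the fixed effects of all efficacy MMRMs. Keep treatment, site, time, treatment-by-time and the baseline covariates. Add a sentence that consistency of the effect across the four sites will be described in one separate model that includes treatment-by-site, with site-specific estimates and confidence intervals.

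If the term is kept in the primary model, name the marginal treatment contrast that carries the test and the site weights it uses. That meets the main concern, although equal weights would still lose precision with unequal sites.

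The cost is a change of wording, with no extra data or participants. The one thing given up is a test of site heterogeneity inside the primary model, and the separate model supplies that information.
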